## 7.2 ASSESSMENT OF ADVERSE EVENTS

Investigators collect and assess adverse events by medical interview, physical examination, and skin diary every study visit. Study physicians assess whether or not participants have adverse drug reactions related to the study drugs. If SAEs and adverse drug reactions are discovered, study physicians record as listed below.

They record diagnosis or event, the day of occurrence, the severity (mild, moderate, or severe), the seriousness (serious or non-serious), the status of the study (continuation, extension, cessation, or stop), the procedure for adverse events (done or not, details if it occurs), the outcome of adverse events (resolved, improved, still present, improved with sequelae, death, unknown, reason if the evaluation is finished with unknown status), the day the physician assesses the status, and relatedness to the study (relatedness denied or relatedness that cannot be denied, evidence of judgment if it is relatedness that cannot be denied).

7.2.1 SEVERITY OF ADVERSE EVENTS

If adverse events are observed, study physicians assess the severity for the most serious condition during the occurrence of the adverse event at three levels, as described below.

1. Mild: signs or symptoms observed that do not need to be treated nor impact on daily activities
2. Moderate: clinical signs or symptoms that need to be treated or impact on daily activities
3. Severe: clinically serious signs or symptoms and events that cause participants to be unable to perform daily activities

7.2.2 OUTCOME OF ADVERSE EVENTS

The outcome of adverse events is assessed at six levels (resolved, improved, still present, improved with sequelae, death, and unknown). If event resolution, improvement, or death is observed, the day of outcome assessment is the day when the event is observed. If the outcome is determined as still present or unknown and participant follow-up to be terminated[[please confirm this meaning]], the day of the outcome assessment is the day when the physicians assess the outcome. Investigators must record the reasons why they remove (terminate) a participant from the study following adverse events or why the adverse events are unknown on the medical chart and eCRF.

7.2.3 SERIOUS ADVERSE EVENTS

Serious adverse events (SAEs) are defined as follows:

1. Death
2. Disability
3. Life-threatening event
4. Disability/incapacity-threatening event
5. Hospitalization, or prolonged existing hospitalization
6. Other serious conditions
7. Congenital or acquired anomaly

For (5), a hospital admission (planned surgery, examination, and so forth) that is planned before the study entry is not included as a hospitalization. However, a new occurrence of an adverse event during the hospitalization is included.

7.2.4 RELATEDNESS TO STUDY INTERVENTIONS

For SAEs, the relatedness to the study intervention is assessed in two categories. If the adverse event is determined to be non-related to the study intervention, the reason is recorded on the medical chart and eCRF.

1. Relatedness can be denied: In cases where it is impossible for the temporal relatedness between adverse event development and study treatment or when the cause of adverse event development can be reasonably explained medically except for study treatment
2. Relatedness cannot be denied: adverse events that are not applicable as above

## 7.3 REPORTING OF ADVERSE EVENTS

Both SAEs that are considered to be related to the study intervention and SAEs that are considered to be unrelated to the study intervention will be reported to the Pharmaceuticals and Medical Devices Safety Information Reporting System [Article 68 of the Pharmaceutical Affairs Law as applied under Article 10(2)]. Principal study investigator reports to the Minister of Health, Labor and Welfare if a serious adverse event is unpredictable and the direct relatedness to the study cannot be denied. In addition, study physicians report spontaneously to the manufacturer in accordance with the provisions of each research implementation facility for the purpose of cooperating with the manufacturer 's voluntary report [Article 68 of the Pharmaceutical Affairs Law as applied under Article 10(1)]. Investigators will input the SAE and adverse drug reaction information into the medical chart and the eCRF.

7.3.1 IMMEDIATE REPORTING OF ADVERSE EVENTS

SAEs (7.2.3) will be reported immediately. If an SAE is observed, study physicians will report the SAE to the head of each study investigational site. The head of the study investigational site must fill out and submit the immediate adverse event report (supplement 3) (or another official document of each investigational site) to the head of each institute and study-coordinating center by email within 72 hours. Study physicians must fill out and email the serious adverse event report (supplement 4) to the study-coordinating center and the data center within 7 days. The study-coordinating center will report the serious adverse event report to the principle investigator and data center.

7.3.2 ROUTINE REPORTING OF ADVERSE EVENTS

If adverse events that are subject to routine reporting are observed, study physicians will input the event information into the eCRF. All events are followed until the event outcome becomes clear and is input into the CRF. If the event cannot be followed for some reason, the study physicians will record the reason on the medical chart and the eCRF.

7.3.3 REPORTING TO THE INDEPENDENT DATA MONITORING COMMITTEE

The study-coordinating center will email the SAE reported from investigational sites immediately to the independent data monitoring committee (IDMC) as soon as the study-coordinating center recognizes the SAEs, and they will ask the IDMC to investigate whether consideration and action in response to the SAE is appropriate. The IDMC investigates the reports and makes a recommendation about the SAEs to the principal investigator. The principal investigator makes a decision regarding study continuation and informs the investigational sites immediately of the decision. If the principal investigator temporarily stops recruitment into the study, he/she will immediately inform the investigational sites of this information and take action.

# 8 ENDPOINTS

## 8.1 PRIMARY ENDPOINT

1. Oral food challenge-proven IgE-mediated hen’s egg allergy at the age of 28 weeks

Justification for the primary endpoint

This study evaluates the presence of IgE-mediated hen’s egg allergy as primary endpoint because hen’s egg is the most common causal FA in Japan.

The timing of oral food challenge tests for hen’s egg is set at the age of 28 weeks because we decided to make a recommendation for participants in our study to ingest hen’s egg starting at 6 months of age based on the past study results reported by Natsume *et al.*

A double-blind, placebo-controlled oral food challenge is the gold standard for diagnosis of IgE-mediated FA to reduce complaints by patients and psychogenic reactions. Because the participants in our study are infants who are at the age of 28 weeks, they are very unlikely to show subjective complains and it is rare that psychological reaction has an effect on the evaluation for OFC. An open method of a food challenge test is common among infants under 1 year old. An open method of a food challenge test can be performed easily, and it results in less of a burden for infants and their caregivers and is expected to be an adequate reliable assessment. Therefore, we decided to use an open method for oral food challenge tests in the study.

## 8.2 SECONDARY ENDPOINTS

EFFICACY ENDPOINTS

1. Food challenge test scores at the age of 28 weeks
2. Total IgE antibody titer in serum at the age of 28 weeks
3. Egg white, ovomucoid, milk, soy, wheat, and peanut-specific IgE antibody titers in serum at the age of 28 weeks
4. Egg white, ovomucoid, milk, soy, wheat, and peanut-specific IgG4 antibody titers in serum at the age of 28 weeks
5. Eczema Area and Severity Index (EASI) scores at 2, 4, and 8 weeks after study entry and at the age of 28 weeks
6. Patient Oriented Eczema Measure (POEM) scores weekly through the study
7. Percentage of disease-free days throughout the study
8. Dose of rescue medication used throughout the duration of the study
9. Infants’ Dermatitis Quality of Life Questionnaire (IDQoL) at 2, 4, and 8 weeks after study entry and at 28 weeks of age
10. Family Impact of Childhood Eczema Questionnaire (DFI) at 2, 4, and 8 weeks after study entry and at 28 weeks of age
11. Cumulative incidence of IgE-mediated FA assessed by a doctor’s interview during the study
12. Cumulative incidence of wheezing assessed by a doctor’s interview during the study

Justification for secondary endpoints (efficacy)

(1) Scoring of the food challenge test has already been recommended in the American Academy of Allergy, Asthma & Immunology – European Academy of Allergy and Clinical Immunology PRACTALL consensus report (65).

(2) (3) To evaluate allergy sensitization

(4) To evaluate immune tolerance against hen’s egg

(5) (6) To evaluate the activity and severity of AD

(7) (8) To evaluate the disease control

(9) (10) To evaluate the QoL

(11) To evaluate the prevalence of other IgE-mediated FA except hen’s egg

(12) To evaluate the prevalence of signs related to asthma

SECONDARY ENDPOINTS (SAFETY)

1. Serious adverse events
2. Adverse drug reactions
3. Salivary cortisol concentrations at 2, 4, and 8 weeks after study entry and at the age of 28 weeks
4. Body weight and body height at the age of 28 weeks

Justification for secondary endpoints (safety)

(1) (2) To evaluate safety of the study drugs

(3) To evaluate the effect on adrenal function by adverse drug reactions to TCSs

(4) To evaluate the effect of adverse drug reactions to TCSs on growth

ADHERENCE EVALUATION

(1) TCS adherence index in accordance with the protocol

(2) Dose of TCS used during the study

Justification for adherence evaluations

(1)(2) To evaluate adherence to the protocol

# 9 STATISTICS

## 9.1 SAMPLE SIZE

For sample size calculation, the proportion of egg allergy in early aggressive intervention and conventional treatment groups are estimated to be 20% and 30%, respectively. With a one-sided significance level of 0.025, 581 participants are needed to provide 80% statistical power. One interim analysis examining efficacy and safety is planned when almost half the participants are finished their trial assessment. Considering the interim analysis, 614 participants are needed. We expect a drop of about 5%, and set the target number of study participants to 650.

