5.1.3 ANTICIPATED PARTICIPANTS AND STUDY DURATION

Anticipated number of participants: N=650 (aggressive intervention group: n=325 and conventional treatment group: n=325)

Duration of the study registration: 2 years from the day of IRB approval

Duration of the study intervention: 3 years after IRB approval

The study duration will be from study entry until completion of primary outcome assessment or until study termination. During the study duration, study treatment is continued unless the study treatment discontinuance criteria are satisfied. The study duration will be postponed under IRB approval if the study is not completed as scheduled.

Justification for the anticipated number of participants

Palmer *et al.* performed a double-blind, randomized controlled trial for infants with AD to test whether or not one-sixth of a raw whole egg taken every day can prevent development of IgE-mediated egg allergy. The infants were allocated to receive 1 teaspoon of pasteurized raw whole egg powder (n=49) or rice powder (n=37) daily from 4 to 8 months of age (67). A high proportion (31% [15/49]) of infants randomized to receive egg had an allergic reaction to the egg powder and 20% (10/49) had a reaction at the first ingestion of egg powder (one-sixth of a raw whole egg) at 4 months of age. When the control group participants received half of a raw egg provocation test at 12 months, 51% (18/35) were diagnosed with IgE-mediated egg allergy. These data suggested that prevalence of egg allergy in infancy is likely to depend on the provocation dose of egg and the preparation of egg such as heated or raw, and also on age and race of the participant. Therefore, we estimate that at least 30% of the participants in the conventional treatment group in this study will be diagnosed with IgE-mediated hen’s egg allergy using an oral food challenge test at the age of 28 weeks. However, the prevalence of IgE-mediated hen’s egg allergy among infants treated with early aggressive intervention for AD has never been reported. In Japan, it is common that infants at the age of 28 weeks do not eat hen’s eggs, and the prevalence of hen’s egg allergy at the age of 28 weeks in Japan is unclear. We consider a clinically effective prevalence of infants with early aggressive intervention for AD to be 20%. As discussed above, the calculated sample size is 614. Taking into consideration that the rate of drop out is about 5%, we determined the anticipated number to be 650.

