9.3.2 PRIMARY ENDPOINT ANALYSIS

Statistical analysis will be performed following the intention to treat (ITT) principle, where participants will be analyzed as they were randomized, not as they were treated. The primary analysis is performed using FAS, and secondarily using PPS. The participants who have missing data for the presence of IgE-mediated hen’s egg allergy are defined as having IgE-mediated hen’s egg allergy and included in the FAS analysis. The participants who have missing data for the presence of IgE-mediated hen’s egg allergy are excluded from the PPS analysis. To verify the study hypothesis, “the aggressive intervention group has lower prevalence of IgE-mediated hen’s egg allergy compared to the conventional treatment group”, the main comparison is the null hypothesis that the percentage of IgE-mediated hen’s egg allergy is higher in the aggressive treatment group than in the conventional group" and the alternative hypothesis is that the percentage of IgE-mediated hen’s egg allergy is lower in the aggressive treatment group than in the conventional group. The *p* value is calculated by the difference in percentage with a one-sided test. The significance level is 0.025. The difference and ratio of these proportions and their 95% confidence intervals for each intervention group will also be calculated.

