9.3.4 INTERIM ANALYSIS

Interim analysis is conducted with the aim of preventing disadvantages to participants due to excessive efficacy and safety procedures unintended in study treatment. The interim analysis is performed when almost half of the participants finish their assessments for the primary endpoint. The interim analysis is done for primary endpoint and safety endpoints. The study registration for study participants does not stop while conducting the interim analysis. The analysis of primary endpoint is performed along with 9.3.2 primary endpoints analysis. The stopping boundary for the analysis of primary endpoint will be calculated based on the O’Brien–Fleming type with a Lan–DeMets α and βspending function at the actual information time. For example, the significance levels of effective discontinuation and invalid discontinuation are 0.0015 and 0.2883, respectively, with the interim analysis for 307 participants who are half of the planned study participants. The interim analysis is conducted by a trial statistician of the interim analysis under a closed situation. The statistician prepares a report of interim analysis results and submits it to the independent data monitoring committee. The results of the interim analysis will be evaluated by the members of the independent data monitoring committee to investigate whether or not the study continues, and the investigation result report is submitted to the principle investigator.

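### The 5% drop-out allowance in 9.1 treats drop-outs as lost, but the primary analysis counts missing challenge results as allergic, so power at N=650 is about 75–77%, not 80%, unless almost none are imputed

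*Protocol*

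**What the plan says.** Protocol 9.1 builds the sample size in three steps.

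- **Rates:** "the proportion of egg allergy in early aggressive intervention and conventional treatment groups are estimated to be 20% and 30%, respectively".
- **Fixed design:** "With a one-sided significance level of 0.025, 581 participants are needed to provide 80% statistical power".
- **Interim and drop-out:** "Considering the interim analysis, 614 participants are needed", followed by "We expect a drop of about 5%, and set the target number of study participants to 650".

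Section 5.1.3 gives the same reason for the last step: "Taking into consideration that the rate of drop out is about 5%, we determined the anticipated number to be 650".

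Section 9.3.2 makes the FAS the primary analysis set. It says that participants whose egg-allergy outcome is missing "are defined as having IgE-mediated hen’s egg allergy and included in the FAS analysis".

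Section 9.2 removes three kinds of randomised infant from the FAS: those who never received the intervention, those with no data after treatment started, and those later found to breach the eligibility criteria.

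Section 9.3.4 sets the interim boundaries as "O’Brien–Fleming type with a Lan–DeMets α and βspending function at the actual information time". For a look at 307 participants, "the significance levels of effective discontinuation and invalid discontinuation are 0.0015 and 0.2883, respectively".

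**The concern.** Dividing a required number by one minus the drop-out rate is right when drop-outs disappear from the analysis and the remaining infants still show the planned contrast. Section 9.3.2 treats them differently. An infant who is in the FAS but has no challenge result stays in the denominator and counts as an event, in either arm. This moves both rates towards 100%, shrinks the difference and increases the variance. Neither 9.1 nor 5.1.3 adjusts the 20% and 30% for it.

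The stated power is therefore not the power of the primary analysis as written. At the planned effect, the chance of missing a real benefit could be about 25% rather than 20%.

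**Working it through.** **Inputs.** Rates 20% and 30%, one-sided 0.025, 80% power, about 5% drop-out and N = 650 (9.1); 1:1 allocation, so 325 per arm (5.3); one look at half information with O'Brien–Fleming-type alpha and beta spending (9.3.4); missing scored as allergic (9.3.2).

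**1. Reproduce the plan's figures.**

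- Fixed design, unpooled variance: N = 2 × (1.960 + 0.8416)² × (0.20×0.80 + 0.30×0.70) / 0.10² = 580.8, so 581 as stated.
- Interim: Lan–DeMets O'Brien–Fleming-type spending at 50% information, with non-binding futility, gives an efficacy boundary z = 2.963 (p = 0.0015), a futility boundary z = 0.559 (p = 0.288) and a final critical value of 1.969. The inflation factor is 1.056, and 580.8 × 1.056 = 613.3, so 614 as stated. The interim levels agree with the stated 0.0015 and 0.2883.
- Drop-out: 614 / 0.95 = 646.3, so 647, set at 650.

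The whole chain reproduces.

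**2. Apply 9.3.2 with all 5% in the FAS and missing, equally in both arms.**

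- Aggressive arm: 0.95 × 20% + 5% = 24.0%.
- Conventional arm: 0.95 × 30% + 5% = 33.5%.
- Difference: 9.5 points.
- Drift: 0.095 / √[(0.24×0.76 + 0.335×0.665) / 325] = 2.691.
- Power with the boundaries from step 1: 74.5%. If the futility boundary is not followed, it is 76.6%.
- Power ignoring the interim: Φ(2.691 − 1.960) = 0.7675, about 77%.

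**3. Vary how much of the 5% is imputed.** If a fraction f of the 5% is imputed and the rest leaves the FAS, then N = 650 × [1 − 0.05(1 − f)], the imputed share is k = 0.05f / [1 − 0.05(1 − f)], and each rate becomes p(1 − k) + k.

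| Share of the 5% imputed | N in FAS | Rates | Power with interim |
|---|---|---|---|
| None | 618 | 20.0% v 30.0% | 80.3% |
| Half | 634 | 22.1% v 31.8% | 77.3% |
| All | 650 | 24.0% v 33.5% | 74.5% |

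**4. Vary the missing rate, all imputed.** Power is 77.6% at 3%, 69.9% at 8% and 66.8% at 10%.

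**5. Other conventions.** With all 5% imputed, pooled or unpooled variance, binding or non-binding futility, and futility followed or not give a range of 74.0% to 77.5%.

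**The case against.** **Not every drop-out is imputed.** Section 9.2 removes some infants from the FAS, and the protocol does not define a drop-out as an infant in the FAS without a challenge result. This stands: 74.5% is the low end of a range from 74.5% to 80.3%, and the split is not given. But the schedule in 6.1 has visits at 2, 4 and 8 weeks and weekly caregiver scores before the challenge. Most infants lost after those visits would have some data, stay in the FAS and be imputed. The top of the range is the less likely end.

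**The planning rates are guesses.** Section 5.1.3 calls 30% a minimum, says that prevalence at 28 weeks in Japan is unclear, and says that none has been reported under the intervention. With all 5% imputed, 20% v 31% gives 81.8% and 19% v 30% gives 82.6%, so a one-point shift would restore 80%. A one-point shift the other way (20% v 29% or 21% v 30%) gives only 71–72% even with nothing imputed. This puts the size of the loss in proportion. It does not make the stated power true at the stated rates.

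**The rule is conservative.** With equal missingness, it dilutes the difference and does not favour the intervention. That is correct, and the validity of a positive result is not in question. The point concerns only the power claimed.

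**Two stronger readings that a reader might infer.** One is that the sample-size arithmetic is wrong. It is not: 581, 614, 650 and both interim levels reproduce. The other is that the rule of scoring missing results as allergic must be dropped from the primary analysis. The documents do not support that. It is a prespecified worst-case rule under an intention-to-treat heading. Analysing observed results only would drop randomised infants and would assume that missingness is unrelated to outcome. Recovering power is not a good reason to change it.

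**Conclusion.** The point holds as a mismatch between two stated parts of the protocol. The drop-out allowance in 9.1 and 5.1.3 assumes loss from the analysis; the primary analysis in 9.3.2 assumes imputation as an event. The shortfall against 80% is about 5.5 points if all 5% are imputed and about 3 points if half are; it vanishes only if essentially none are.

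These figures assume equal missingness in the two arms, 20% and 30% as true challenge-proven rates before imputation (which is how 5.1.3 derives the 30%), 5% missing, and the interim boundaries followed as in 9.3.4. More missing data would lower the power further.

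**What to change.** In 9.1, and in the matching paragraph of 5.1.3, restate the power at N = 650 under the 9.3.2 rule: about 75% if all 5% remain in the FAS with a missing result, and about 77% if half do. State the assumed split between infants excluded from the FAS under 9.2 and infants imputed as allergic, and that missingness is taken as equal in both arms.

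This is a change of wording, with no extra enrolment and no change to the analysis. Its cost is a less favourable stated power.

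Making a different missing-data rule primary and keeping the present one as a sensitivity analysis is an option, not a requirement. It is a trade-off. Because it affects the primary endpoint, 17.4.1 would class it as an amendment needing steering committee and IRB approval. If chosen, it should be settled before anyone sees unblinded results.

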## 9.2 ANALYSIS SET

The following data set is used for analysis. The target analysis of the primary endpoint of efficacy is defined as Full Analysis Set (FAS).

1. Full Analysis Set (FAS)

The group excluding the participants as follows from all the participants who are randomized

- - Participants who have never received intervention
  - Participants who have not yielded data after the start of the study treatment
  - Participants who are found to have violated eligibility criteria after received intervention t

1. Per Protocol Set (PPS)

Of the FAS, the group consisting of participants without significant deviation from the implementation plan

1. Target group for safety analysis

The group consisting of all participants who have undergone the study treatment at least once

